## 3.4 Statistical Methods

Sample Size Determination:

The study has been designed to confirm that KindaPed AF (5% 1,2-octanediol alcohol free lotion) has an essentially similar efficacy comparable to that of KindaPed lotion (5% 1,2-octanediol with 20% alcohol). It is not designed as a full equivalence study but is designed to be able to identify any significant differences between the treatments in pair wise comparisons.

This study is based upon the same sample size as that used in four previous studies of head louse treatments conducted on behalf of Thornton & Ross Ltd (CTMK06, CTMK08, CTMK09, and CTMK10) for basic comparative purposes and is estimated to provide adequate data for demonstration of effect. The actual sample size of 40 per group makes allowance for dropout. Comparison of the results from this study can be made with the results from those studies with respect to similarities of population demographics, and with previous studies of 1,2-octandiol lotion (CTEP01 and CTEP02) with respect to efficacy outcome and acceptability.

Interim analysis

It is proposed to conduct an interim analysis of treatment outcome only after enrolment and completion of sixty (60) participants (approximately 20 in each group). This analysis will be conducted blind of treatment allocation using outcome data entered into a spreadsheet which would then be overlaid with treatment allocation identified only as “a”, “b”, or “c”. This will enable the Sponsor to identify whether one treatment is performing exceptionally well or exceptionally poorly and allow them to make a decision in good time whether they wish to extend or to curtail any aspect of the study. The results of this analysis will be conveyed to the Sponsor in narrative form only.

Analytical Methods:

The primary endpoint is the frequency of cure tested using the "intention-to-treat" population in comparison with the body of data obtained during previous studies using overnight or 2-2.5 hour application times for the product. Secondary endpoints will be the frequency of ovicidal failure and of reinfestation and the numbers of lice seen at the different assessment times. Other endpoints will be the safety of the product and participant acceptance.

Analyses will be conducted based on both the "intention-to-treat" and the "per-protocol" populations. The study group will be compared with study groups from previous studies in which participants were treated using an 8 hour/overnight treatment or a 2-2.5 hour treatment on baseline characteristics, safety, acceptability, and efficacy using Fisher's exact test for yes/no variables and the Mann-Whitney U test for ranked variables. Where analysis shows important differences in baseline characteristics, chi squared and rank tests stratified for these characteristics may also be conducted. 95% confidence limits will be presented for the difference between this study group and previous groups in the primary endpoint.

These analyses will be used to determine whether the study provides evidence of essential similarity between KindaPed AF (5% 1,2-octanediol alcohol free lotion) and KindaPed (5% 1,2-octanediol lotion) in the elimination of infestation.

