**Aims of the Study:** To obtain directly comparative information to show that KindaPed AF 5% 1,2-octanediol alcohol free lotion is equally effective in the eradication of head lice as KindaPed 1,2-octanediol lotion.

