## 1.2 Rationale

Infestation with the human head louse (*Pediculus capitis*) has been at a high level within the European Union since the appearance of strains of head lice resistant to one or more of the currently available insecticidal products were first described (1, 2, 3). Families are aware of a resistance problem but have no way of knowing if the lice they are trying to eradicate are resistant to the product they are using. Many people have attempted alternative methods of treatment such as combing (4) but for the most hard pressed families (as described in reference 3) this frequently has a poor outcome with children suffering infestations for many months (5).

Given a choice, a majority of care givers would choose to use a safe and simple chemical treatment to eliminate infestation form their children. Various products have been introduced into the European market as class I Medical Devices based on their physical mode of action and their general safety profile.

KindaPed (5% 1,2-octanediol lotion) and KindaPed AF (5% 1,2-octanediol alcohol free lotion) are class I Medical Device preparations based upon a cosmetic moistening and spreading agent.

The original KindaPed (5% 1,2-octanediol lotion) was originally investigated in a large randomised controlled trial in 2007-08 in comparison with 0.5% malathion liquid. In this study KindaPed was shown to be significantly superior to malathion using applications times of 2-2.5 hours and 8 hours/overnight. However, the KindaPed preparation was formulated with 20% isopropanol, which it is believed was the cause of a number of mild adverse reactions on excoriated skin.

KindaPed AF (5% 1,2-octanediol alcohol free lotion) contains no alcohol and should not cause irritation even on excoriated skin. This clinical investigation is designed to confirm no loss of efficacy of Kindaped AF versus Kindaped.

Both 5% 1,2-octanediol lotion preparations are used with a repeat treatment applied after one week as recommended by The British National Formulary (BNF) for all currently available treatments.

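### Similarity of KindaPed AF to KindaPed is to be judged without any margin, in a 40-per-group design described as difference-finding that misses a true 20-point deficit in about 35-63% of trials

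*Protocol*

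**What the plan says.** The claim is one of similarity throughout. The aims in Protocol section 1.1 are to show that KindaPed AF "is equally effective in the eradication of head lice as KindaPed 1,2-octanediol lotion". Section 1.2 says: "This clinical investigation is designed to confirm no loss of efficacy of Kindaped AF versus Kindaped". Section 3.4 opens by saying that the study was designed to confirm that AF "has an essentially similar efficacy comparable to that of KindaPed lotion".

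The next sentence of section 3.4 describes a different kind of study: "It is not designed as a full equivalence study but is designed to be able to identify any significant differences between the treatments", in pairwise comparisons. The size of 40 per group is carried over from four previous studies and is said to allow for dropout. No cure rate, difference, significance level, power or margin goes with it.

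The analysis text in section 3.4 names "Fisher's exact test for yes/no variables", the Mann-Whitney U test for ranked variables and 95% confidence limits, in both the intention-to-treat and per-protocol populations. The comparison it describes for the tests and the limits is between this study's group and groups from previous studies. It ends: "These analyses will be used to determine whether the study provides evidence of essential similarity".

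**The concern.** A conclusion of no loss of efficacy needs a criterion: the largest deficit in cure that would still count as similar, and an interval that excludes anything larger. The protocol has neither for A versus C. It offers tests that look for a difference, limits with nothing to read them against, and an assurance that the size can find differences.

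If the trial shows no significant difference, nothing in the plan stops that result from being reported as evidence of similarity. Small trials produce such results easily, so the claim becomes easier to make as the trial becomes smaller or noisier. A materially less effective formulation could be described as equally effective. The interim analysis in section 3.4 adds to this: the sponsor may extend or curtail the study after 60 participants, so a criterion chosen later could be influenced by the data.

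**Working it through.** **The plan's own figure.** Only 3 x 40 = 120 can be checked. The 40 per group cannot be reproduced, because its inputs are not given.

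**Inputs.** From the protocol: 40 per group, equal allocation, Fisher's exact test for cure. Assumed: two-sided 5% (suggested by the 95% limits) and a KindaPed cure rate of 70-95% (no rate is given, so a range is shown).

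**Step 1: power of Fisher's test, 40 v 40.** Power = sum over all (a, c) of Bin(a; 40, p - d) x Bin(c; 40, p) x 1[Fisher p-value <= 0.05], where p is the KindaPed cure rate, d the true deficit with AF, and a and c the numbers cured on AF and KindaPed. Full enumeration gives:

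| KindaPed cure | Power, d = 10 points | d = 15 | d = 20 | d giving 80% power |
|---|---|---|---|---|
| 95% | 18% | 41% | 65% | 24.5 points |
| 90% | 16% | 33% | 53% | 28 |
| 85% | 14% | 28% | 46% | 30.5 |
| 80% | 12% | 25% | 41% | 32 |
| 75% | 11% | 22% | 38% | 32.5 |
| 70% | 11% | 21% | 37% | 33 |

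A true 20-point deficit is therefore missed in 100 - 65 = 35% to 100 - 37 = 63% of trials. The result is not sensitive to the exact group size: power for 20 points is 31-57% at 36 per group and 40-70% at 44 per group (11 blocks of 12 = 132 allocations, 132 / 3 = 44).

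**Step 2: width of the 95% limits when the observed rates are identical.** With Newcombe's method and equal observed rates p, the half-width is sqrt((p - l)^2 + (u - p)^2), where l and u are the Wilson limits for one group. For 36/40, l = 0.769 and u = 0.960, so the half-width is sqrt(0.131^2 + 0.060^2) = 0.144. At 38/40 each it is 12 points, and at 28/40 each 20 points. Even a perfect match leaves deficits of about 12-20 points open.

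**Step 3: observed 20-point deficits.** 26/40 v 34/40 gives Fisher p = 0.069 with Newcombe limits of -37 to -1 points. 28 v 36 gives p = 0.048, and 30 v 38 gives p = 0.025. Whether an observed 20-point deficit reaches significance depends on the cure rate.

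**Step 4: what 40 per group could support with a margin M.** With equal true rates p, one-sided 2.5% and 80% power, n per group = (1.960 + 0.842)^2 x 2p(1 - p) / M^2. For p = 0.90 and M = 0.20: 7.85 x 0.18 / 0.04 = 35.3, so 36.

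| KindaPed cure | M = 10 points | M = 15 | M = 20 |
|---|---|---|---|
| 95% | 75 | 34 | 19 |
| 90% | 142 | 63 | 36 |
| 85% | 201 | 89 | 51 |
| 80% | 252 | 112 | 63 |
| 70% | 330 | 147 | 83 |

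Of the cases tabulated, 40 per group suffices only for 15 points at 95% cure, or 20 points at 90% or above.

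**The case against.** Several points on the other side deserve weight.

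- **No rule equating non-significance with similarity is written down.** A reader might infer one from the aims and the tests, but the documents do not state it. The 95% limits, in both populations, are among the analyses meant to decide similarity, so the tests are not the only tools. This stands. The defect is that neither tests nor limits have a criterion.
- **The protocol disclaims full equivalence.** It does, and that is candid. But the disclaimer does not fit with aims of equal effectiveness and confirmed absence of loss.
- **The sentence on identifying differences may mean only that differences will be tested for.** That reading is possible. As part of the sample size justification it still suggests a sensitivity that the size does not have, which is why it is misleading.
- **The 40 v 40 figures do not describe the analysis as written.** Correct: that analysis compares with earlier groups of unstated size. The figures apply to the pairwise comparisons that section 3.4 says the design can serve. The mismatch is part of the problem, since the randomised comparison is the one that bears on the aims.
- **A statistical analysis plan may supply a margin.** It may. The design claim, the basis of the sample size and the intended conclusion are nevertheless stated here, and they do not agree with each other.

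Two stronger readings should be resisted. A reader might infer that any 20-point deficit will be non-significant; Step 3 shows that this fails at an observed KindaPed cure of 90% or 95%. A reader might also infer that multiple pairwise testing makes the similarity claim too easy; false differences work against such a claim, so multiplicity does not support the harm described.

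**Conclusion.** The concern holds in this form. The protocol sets out to confirm similarity with a design that it describes as difference-finding, fixes no margin, writes its confidence limits against previous studies instead of group C, and uses a size with no stated power. At that size the absence of a significant difference says little, even about large deficits, so it cannot support similarity. The size of the problem rests on the assumed two-sided 5% level and the assumed cure range. The missing criterion and the mismatch between aim and design rest on neither. It should be corrected before the interim analysis, because it governs the trial's main conclusion.

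**What to change.** 1. In the sample size text of section 3.4, replace the statement about identifying differences with what the size can do: 80% power only for differences of about 25-33 points, and 95% limits of about +/-12 to 20 points when observed rates are equal, for an assumed KindaPed cure of 70-95%.
2. Name randomised A versus C, which share the same application time, as the primary comparison. Rest any conclusion of no loss of efficacy or essential similarity on the lower 95% limit for A minus C in cure, read against a justified margin fixed before the interim analysis, in both the intention-to-treat and per-protocol populations. Comparisons with earlier studies then become supportive.
3. If no margin is set, or it is not met, remove the wording on confirming and on equal effectiveness, report the estimate with its interval, and state which deficits are not excluded.

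The cost is protocol wording and a less favourable claim. No patients are added, unless the sponsor wants power for a margin that 40 per group cannot support. As Step 4 shows, that size suits only a wide margin at high cure rates.

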## 4.14 Early Termination of the Study

By agreement between Thornton & Ross Ltd and the Principal Investigators, the study may be terminated at any time if the recruitment rate is such that the required number of participants will not be recruited within the specified time, if the product being used is deemed to be failing unacceptably, or if any safety concerns arise.

5. Appendix 1: Declaration of Helsinki

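### The interim look lets the sponsor resize the trial on by-arm outcomes, yet the final analysis assumes a fixed size; a curtailed trial could easily be read as showing similarity

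*Protocol*

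**What the plan says.** Protocol section 3.4 sets the look "after enrolment and completion of sixty (60) participants (approximately 20 in each group"). It describes the analysis as blind: "This analysis will be conducted blind of treatment allocation using outcome data entered into a spreadsheet". The arms are then added to those data under the coded labels a, b and c. The purpose is to let the sponsor "identify whether one treatment is performing exceptionally well or exceptionally poorly" and, on that basis, to "allow them to make a decision in good time whether they wish to extend or to curtail any aspect of the study". One limit is placed on what the sponsor receives: "The results of this analysis will be conveyed to the Sponsor in narrative form only".

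On size, the section says "The actual sample size of 40 per group makes allowance for dropout". It gives no alpha, power, cure rate or margin. It says that the study is not a full equivalence design but should detect significant differences between the three groups taken in pairs.

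The analytical methods in the same section are Fisher's exact test, the Mann-Whitney test and 95% confidence limits. These are to determine whether the two products are essentially similar. They make no reference to the interim look. The limits are described as being for the difference from groups in earlier studies.

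Section 4.14 separately allows termination, among other grounds, "if the product being used is deemed to be failing unacceptably".

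**The concern.** Coding the arms as a, b and c hides their names but not the comparison. To say that one treatment stands out, the outcomes of the three arms must be set against each other. The decision that follows is open: any aspect of the study may grow or shrink. The final tests and limits are those of a trial whose size did not depend on its results.

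Two things are at stake. First, the trial exists to show that the alcohol-free lotion is as effective as the original. There is no margin, so the natural reading of a non-significant result is that the products are similar, and cutting the trial short makes such a result more likely whatever the truth. Second, if a difference could be declared at either look, or after an extension chosen because of by-arm results, the chance of a false difference can exceed the nominal level.

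**Working it through.** **Inputs from section 3.4.** Three groups, 120 in total, look at 60. So 120/3 = 40 per group at the end, 60/3 = 20 per group at the look, and the information fraction is 20/40 = 0.5. The protocol states no power or error rate that could be reproduced.

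**Assumptions.** Two-sided 5%; true cure 85% for the interval; 20-point losses for power; common cure rates of 70 to 90% for false differences.

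**1. Precision if the trial is curtailed.** The Newcombe interval combines the Wilson limits (l, u) of each arm. With equal observed proportions p, the half-width is √[(p − l)² + (u − p)²].
- 17/20 in each arm: Wilson limits 0.640 and 0.948; half-width √(0.210² + 0.098²) = 0.232, about ±23 points.
- 34/40 in each arm: Wilson limits 0.709 and 0.929; half-width √(0.141² + 0.079²) = 0.162, about ±16 points.

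**2. Power of Fisher's exact test.** Sum the binomial probabilities of all pairs of cure counts for which Fisher p ≤ 0.05.

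| True cure | 20 per group | 40 per group |
|---|---|---|
| 85% v 65% | 21% | 46% |
| 90% v 70% | 24% | 53% |
| 80% v 60% | 19% | 41% |

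At 85% v 65%, the result is non-significant in 1 − 0.21 = 79% of trials curtailed at 20 per group, against 1 − 0.46 = 54% at 40. In counts: at 20 per group, 17 cures v 11 gives p = 0.08 and 17 v 10 gives p = 0.04. The observed gap must therefore reach 7/20 = 35 points before it is significant. At 40 per group, 34 v 26 gives p = 0.07 and 34 v 25 gives p = 0.04, a gap of 9/40 = 22.5 points.

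**3. False differences.** Simulation with equal cure rates, Fisher's test at 5%, and a claim allowed at 20 or at 40 per group. Ranges cover cure rates of 70 to 90%, rounded to about half a point.

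| | One look at 40 | Looks at 20 and 40 |
|---|---|---|
| One pair | about 1.5 to 3% | about 2.5 to 4.5% |
| Any of three pairs | about 4.5 to 7% | about 6.5 to 11% |

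Part of the last row is multiplicity across pairs. The look adds the difference between its two columns.

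**4. Coverage.** A nominal 95% Wald interval for the difference between two of the trial's arms covers in 94.1 to 94.8% of trials at a fixed 40 per group. If the trial stops at 20 whenever those arms differ by at least 5 cures, or by at least 6 (an illustrative rule, since the protocol gives none), coverage is 90.7 to 93.9%.

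**The case against.** The protocol plans no significance test and no declaration of difference or similarity at the look. The sponsor receives a narrative, not a table. Curtailing for poor results alone does not raise the false-positive rate. Fisher's test is conservative enough that one pair stays below 5% even with two looks. An analysis plan that is not shown may hold boundaries and name who runs the look. Section 4.14 is an ordinary termination clause that also covers recruitment and safety. The 95% limits are described against earlier studies, not between the trial's own arms.

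Most of this stands, and it limits the point. Some stronger readings are tempting but not supported:
- A reader might apply the textbook 8.3% for two unadjusted looks, or 10.3% with an added extension. Both are normal-theory figures that need an early claim at the look, and the second has the extension decided at 40 per group. The protocol states neither, and it plans Fisher's test. Extending at the look to 60 per group whenever |z| > 1, with a single final test, gives 4.3% even under normal theory.
- A reader might infer that staff who know one allocation could decode a label, or that trends would reach the assessors. The protocol names only the sponsor as recipient, in narrative form, and assessors are different people from those who apply treatment. It does not say that either group sees the coded spreadsheet.
- A reader might infer that similarity may be claimed at the look. The text does not say so; it merely leaves a curtailed comparison open to that reading.

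What remains is the text itself. Section 3.4 grants the sponsor open discretion on by-arm information. An analysis plan could restrict that only by departing from the protocol. The narrative must still say whether an arm stands out, or it would not serve its stated purpose.

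**Conclusion.** The point holds as a should-fix. The protocol allows an unrestricted change to the trial on by-arm outcomes and then analyses the data as a fixed design, so nominal error rates and coverage are not guaranteed. It would be too strong to say that they are lost, because the effect depends on what the sponsor does.

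The firmest consequence concerns similarity: a trial cut to about 20 per group would miss a 20-point loss about four times in five (85% v 65%). Excess false differences arise clearly only when early claims are combined with all three pairs, or under some extension rules. All sizes rest on an assumed two-sided 5% and on assumed cure rates, because the protocol gives none. The comparison with earlier studies in section 3.4 is a separate matter and is not judged here.

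**What to change.** Amend the interim paragraph of section 3.4 to state that:
1. The look is operational or futility-only, and no difference or similarity is claimed at it. If an early claim of difference is wanted, it is made only at two-sided p < 0.001, with the final test at 0.05; under normal theory this keeps the overall level per comparison at about 5.0%.
2. 40 per group remains the primary analysis, and any increase in size is decided on pooled outcomes, not by arm.
3. If an arm or the study is curtailed early, the comparison is reported as inconclusive on similarity.
4. The by-arm listing is kept from treating and assessing staff.

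Refer section 4.14 to the same statement where termination rests on efficacy. A look with no early claim and no by-arm extension needs no adjustment of the final 5% level. The cost is a protocol amendment and less sponsor discretion mid-study; no extra participants are needed.

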## Design in Brief

This is a randomised, controlled, assessor blind, study of two variants of the same class I Medical Device product for control of head louse infestation. One hundred and twenty (120) evaluable participants, minimum age 6 months^[[1]](#footnote-1)^, who upon examination are confirmed to have head lice and who fit the selection criteria (see section 2.1.2 and 2.1.3) will be recruited to the study.

At the first visit (Day 0), verbal consent will be obtained to check for the presence of live head lice using a fine-toothed plastic detection comb. After the preliminary assessment, participants can be enrolled to the study, provided they comply with the inclusion/exclusion criteria, and any further questions they may have are fully dealt with.

Participants (or their parents/guardians if they are aged below 16 years) will be asked to give written informed consent and sign a Consent Form before participation in the study. There will be a separate Assent Form for younger children capable of giving written assent. Children too young to give assent can be entered in the study on the consent of a parent/guardian. Assent Forms will be witnessed by the parent/guardian and signed by the Investigator. Consent will be sought for permission to inform the participant’s GP that their patient is taking part in the study. Other infested household members who are unable to participate in the study for any reason, e.g. not being available for the assigned follow up visits, will be offered a standard of care treatment (Hedrin 4% liquid gel) in order to reduce the risk of reinfestation of participants during the course of the study.

The Investigator will assign each participant a study number, this being the next available number allocated to that investigator from a randomised treatment allocation sequence. Participants will be divided between three groups as follows:

Group A: KindaPed AF (5% 1,2-octanediol alcohol free lotion ), applied for 2 hours (maximum 2.5 hours) before washing off using shampoo, with a repeat treatment one week later.

Group B: KindaPed AF (5% 1,2-octanediol alcohol free lotion ), applied for 8 hours (minimum) or overnight before washing off using shampoo, with a repeat treatment one week later.

Group C: KindaPed lotion (5% 1,2-octanediol lotion with 20% alcohol), applied for 2 hours (maximum 2.5 hours) before washing off using shampoo, with a repeat treatment one week later.

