### 2.3.2 Randomisation

The randomised treatment allocation code will be generated using the free online randomisation service provided at <http://www.randomization.com/>. The treatment allocation will be made in 11 balanced blocks of 12 treatments and the Seed number and date of randomisation will be recorded on the randomisation plan.

The treatment allocations will be prepared as sheets bearing the identification of the product to be used and instructions for application of the relevant product. The product identification/instruction sheets will be sealed in opaque envelopes numbered sequentially on the outside with the participant number taken from the randomisation schedule. Each envelope will be enclosed in a CRF prior to use. Each investigator delegated to enrol participants will allocate the numbered CRFs to participants in numerical sequence. However, where two or more investigators, each allocated separate blocks of numbers, enrol participants in parallel the overall numerical sequence will not follow chronologically.

Only after written informed consent has been obtained will the investigator allocate a study number and open the randomisation envelope for that number. The investigating team will keep a second batch of envelopes, and a copy of the randomisation code also in a sealed envelope, in case an adverse event, reaction, or any other emergency circumstance necessitates that the code be broken.

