### 2.3.3 Study Methodology

2.3.3.1 Pre-recruitment

Participants will be invited to join the study via advertising in public media (newspapers, magazines, as appropriate), via posters in schools, pharmacies, GP surgeries, and through letters or telephone calls to families who have expressed an interest in joining further clinical investigations and are listed on a database held at the Medical Entomology Centre. A detailed Participant Information Booklet (PIB) will be provided to explain the purpose of the study. This will include a children’s section explaining what will happen if the person enters the study.

A member of the study team will conduct a brief interview to establish whether the person will be suitable for entry into the study. If the person wishes to enter the study, they will be conducted through a standardised consent procedure. Potential participants must have had access to the PIB for at least 24 hours before the recruitment takes place.

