## 3.3 Proposed Primary and Secondary Analyses

1. To compare efficacy of KindaPed AF (5% 1,2-octanediol alcohol free lotion) with KindaPed (5% octanediol lotion with 20% alcohol) for elimination of infestation by head lice.
2. To compare KindaPed AF (5% 1,2-octanediol alcohol free lotion) with KindaPed (5% octanediol lotion with 20% alcohol) with regard to prevention of louse egg hatching (ovicidal action) by monitoring the presence/absence of juvenile stages of lice following the first and second treatments.
3. To compare KindaPed AF (5% 1,2-octanediol alcohol free lotion) with KindaPed (5% octanediol lotion with 20% alcohol) To investigate 5% 1,2-octanediol alcohol free lotion with regard to participant acceptability.

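### Section 3.4 tests cure, and gives its only confidence limits, against previous studies rather than the randomised KindaPed group, contradicting the protocol's own comparative aim

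*Protocol*

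**What the plan says.** The aim in section 1.1 is "To obtain directly comparative information to show that KindaPed AF 5% 1,2-octanediol alcohol free lotion is equally effective" as KindaPed. Design in Brief sets up three randomised groups. A and B receive KindaPed AF, for 2-2.5 hours and for at least 8 hours or overnight. The third is a concurrent control: "Group C: KindaPed lotion (5% 1,2-octanediol lotion with 20% alcohol), applied for 2 hours (maximum 2.5 hours". Section 2.3.2 fixes the allocation: "The treatment allocation will be made in 11 balanced blocks of 12 treatments".

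Section 3.3 lists, as its first analysis, KindaPed AF against KindaPed "for elimination of infestation by head lice". The sample size text in section 3.4 says the study is "designed to be able to identify any significant differences between the treatments in pair wise comparisons".

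The Analytical Methods in the same section name a different comparator. In the intention-to-treat population, cure is tested "in comparison with the body of data obtained during previous studies using overnight or 2-2.5 hour application times for the product". Fisher's exact and Mann-Whitney tests are assigned to a comparison of the study group, in the singular, with groups from earlier studies. The interval is defined the same way: "95% confidence limits will be presented for the difference between this study group and previous groups in the primary endpoint". The section closes by saying that these analyses will decide whether KindaPed AF and KindaPed are essentially similar.

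**The concern.** The protocol builds a randomised control and then does not use it in the analysis that it describes for the primary endpoint. A statistician following the Analytical Methods literally would report no estimate, test or interval for A versus C or B versus C. The text also cannot be carried out without guessing, because a trial with three randomised groups has no single study group.

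Randomisation makes A and C comparable in everything except formulation. A comparison with earlier studies has no such protection. A difference in cure between periods, whatever its cause, adds directly to the apparent formulation effect. It can produce a difference where none exists, or cancel a real loss of efficacy. Section 1.2 says the trial is there to confirm that efficacy has not been lost, so the second error matters at least as much as the first.

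**Working it through.** **1. The statements side by side.**

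| Place in the protocol | Comparator for KindaPed AF |
|---|---|
| 1.1, aims | KindaPed, direct comparison |
| Design in Brief | Randomised Group C |
| 3.3, item 1 | KindaPed; concurrent or historical not stated |
| 3.4, sample size | The treatments, pairwise |
| 3.4, primary endpoint | Previous studies |
| 3.4, Fisher and Mann-Whitney tests | Groups from previous studies |
| 3.4, 95% limits | Previous groups |
| 3.4, basis of the conclusion | The analyses in the three rows above |

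The first four rows set up or are consistent with a comparison inside the trial. The last four, which say what will be computed, go outside it.

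**2. The protocol's own figures.** 3 × 40 = 120 agrees with the stated total, and 11 × 12 = 132 allocation numbers give 132 / 3 = 44 per group. No power, effect size, cure rate or margin is given, so no power figure can be reproduced.

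**3. The time gap.** Section 1.2 dates the original KindaPed trial to 2007-08. Section 1.1 plans this one for September 2010 to January 2011.

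**4. What drift would do (illustration).** The protocol gives neither cure rates nor the number of historical participants, so the following are assumptions:
- 40 current AF participants with true cure of 80%;
- concurrent KindaPed also at 80%, so there is no formulation effect;
- nH historical KindaPed participants, 40 or 150, with true cure pH.

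The test is the one the protocol names, two-sided Fisher at 5%, enumerated exactly:

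P(significant) = Σi Σj Bin(i; 40, 0.80) × Bin(j; nH, pH) × 1[Fisher p ≤ 0.05]

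| Historical cure pH | Drift | nH = 40 | nH = 150 |
|---|---|---|---|
| 80% | 0 | 3% | 4% |
| 85% | 5 points | 5% | 11% |
| 90% | 10 points | 16% | 36% |
| 95% | 15 points | 41% | 76% |

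Here the historical rate is the higher one, so AF wrongly looks worse. If the historical rate is lower (75%, 70%, 65%), with 40 to 200 historical participants, the figures are about 5-8%, 12-21% and 25-44%, and AF wrongly looks better. More historical data does not help: in this illustration a larger nH makes the test more likely to declare the drift significant.

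The masking case needs no separate calculation. If AF truly cures 15 points fewer than concurrent KindaPed and the historical rate is also 15 points lower, the test compares equal proportions and has no power to see the loss.

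**5. What the randomised contrast would give.** For 40 against 40 with equal cure p, the 95% half-width is 1.96 × √(2p(1 − p)/40). This is ±20.1 points at p = 0.70, ±17.5 at 0.80 and ±13.1 at 0.90. The cure rates are again assumed.

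**The case against.** The strongest reply is that a comparison between randomised groups was plainly intended. Section 3.3 lists AF against KindaPed first, and the sample size text speaks of pairwise comparisons. That is right. A reader might infer from the Analytical Methods that the sponsor decided to discard the randomised control, or that the trial cannot answer its question. The documents do not support either. They show a contradiction between stated intent and described method, and the data to resolve it will be collected. The contradiction still has to be removed, because an analysis plan faithful to the Analytical Methods would inherit the wrong comparator.

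A second reply is that section 3.4 allows stratified tests where baseline characteristics differ importantly. These are optional, can use only recorded characteristics, and cannot remove unmeasured period effects.

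Third, the historical data have a proper use. No concurrent group receives KindaPed for 8 hours or overnight, and section 1.2 says the earlier trial used that application time. Those data are therefore the only KindaPed comparator matched to Group B on exposure. This is a good reason to keep the comparison as support, but not to make it primary.

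Two further inferences should be resisted. One is that the earlier studies differed in place, louse population or assessors: the protocol does not say, and only the calendar gap is documented. The other is that the same people appear in both data sets. Section 2.3.3.1 does recruit, among other routes, from "families who have expressed an interest in joining further clinical investigations and are listed on a database held at the Medical Entomology Centre", but nothing shows that earlier KindaPed participants re-enrolled. The point does not need either.

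Finally, the order of the contrasts (A versus C, B versus C, or both) is a choice that a statistical analysis plan may settle. Its absence here is not a fault.

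**Conclusion.** The point holds as a contradiction that makes the primary analysis wrong as written. Section 3.4 names previous studies as comparator for the primary test and for the only confidence limits, and bases the conclusion on them. The aim, the design, the listed primary analysis and the pairwise statement call for a comparison of the treatments within the trial. This is a stated comparator, not a detail left for later.

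The conclusion rests on the text alone. The drift figures show a mechanism and do not estimate this trial's error rate. They depend on an assumed 80% current cure rate, an assumed 40 to 150 historical participants and the direction of the drift, and for a given drift they vary about two-fold with the historical number alone. Whether any drift exists is unknown.

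**What to change.** Rewrite the Analytical Methods in section 3.4:

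- Primary analysis: the difference in cure proportion, with 95% confidence limits, in the intention-to-treat population, between the randomised AF group or groups and randomised Group C.
- Identify A versus C as the contrast that isolates formulation at equal application time. Report B versus C separately, since it differs in application time as well.
- Replace the singular study group with the named groups throughout, and base the essential-similarity conclusion on the randomised comparison.
- Keep comparisons with CTEP01, CTEP02 and other earlier studies as supportive only, including any comparison of Group B with earlier 8-hour or overnight KindaPed data.

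The cost is a wording change, with no new participants, visits or data. It does not supply a similarity margin or make 40 per group precise: with limits of roughly ±13 to ±20 points at assumed cure rates of 90% to 70%, a non-significant difference would not by itself show similarity. That is a separate matter.
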